## Abstract

**Background:**

Adolescents and young adults (AYA) with chronic somatic conditions have an increased risk of comorbid depression and anxiety symptoms. Internet- and mobile-based cognitive behavioural therapy (iCBT) might be one possibility to extend the access to evidence-based treatments. Studies suggest that guided iCBT can reduce anxiety and depression symptoms in AYA. However, little is known about the effectiveness of iCBT for AYA with chronic somatic conditions and comorbid symptoms of anxiety and/or depression in routine care. Evidence on the (cost-)effectiveness of iCBT is essential for its implementation in health care.

**Objectives and methods:**

This multicentre two-armed randomized controlled trial (RCT) aims to evaluate the (cost-) effectiveness of guided iCBT (youthCOACH_CD_) in addition to treatment as usual (TAU) compared to enhanced treatment as usual (TAU+) in AYA aged 12–21 years with one of three chronic somatic conditions (type 1 diabetes, cystic fibrosis, or juvenile idiopathic arthritis). AYA with one of the chronic somatic conditions and elevated symptoms of anxiety or depression (Patient Health Questionnaire [PHQ-9] and/or Generalized Anxiety Disorder [GAD-7] Screener score ≥ 7) will be eligible for inclusion. We will recruit 212 patients (2 × *n* = 106) in routine care through three German patient registries. Assessments will take place at baseline and at 6 weeks, 3 months, 6 months, and 12 months post-randomization. The primary outcome will be combined depression and anxiety symptom severity as measured with the PHQ Anxiety and Depression Scale. Secondary outcomes will include health-related quality of life, coping strategies, self-efficacy, stress-related personal growth, social support, behavioural activation, adjustment and trauma-related symptoms, automatic thoughts, intervention satisfaction, working alliance, and Internet usage. The cost-effectiveness will be determined, and potential moderators and mediators of intervention effects will be explored.

**Discussion:**

iCBT might implicate novel ways to increase the access to evidence-based interventions in this specific population. The distinct focus on effectiveness and cost-effectiveness of youthCOACH_CD_ in patients with chronic somatic conditions, as well as intervention safety, will most likely provide important new insights in the field of paediatric e-mental health. A particular strength of the present study is its implementation directly into routine collaborative health care. As such, this study will provide important insights for health care policy and stakeholders and indicate how iCBT can be integrated into existing health care systems.

**Trial registration:**

German Clinical Trials Register (DRKS), DRKS00017161. Registered on 17 September 2019.

## Background

On average, 15% of children and adolescents suffer from chronic somatic conditions, and the trend is rising [1]. Disabling conditions are—amongst others—diabetes, with 310/100,000 children and adolescents [2], cystic fibrosis, with 8/100,000 [3], and juvenile idiopathic arthritis, which affects about 100/100,000 [4] individuals at the transition to adulthood. Current studies estimate the average annual social/economic costs of cystic fibrosis to be €53,256 (SD 46,589) [5], juvenile idiopathic arthritis €27,634 (SD 28,008) [6], and type 1 diabetes with €3745 (inter-quartile range 1943–4881) [7] in adolescents and young adults (AYA) per patient.

Mental disturbances and disorders are common in this population, particularly depression- and anxiety- related symptoms [8, 9], which in turn are associated with reduced quality of life, reduced treatment adherence, poorer long-term prognosis [10], and increased health service use (outpatient and inpatient, medical/medical claims, and pharmacy claims) [11].

AYA with chronic somatic conditions are confronted with two challenges simultaneously: disease-specific requirements (e.g. medication, visits to a physician, physical limitations, etc.) and age-specific developmental tasks (e.g. development of identity and autonomy) [9]. Hence, a significant part of AYA with chronic somatic conditions are in need of mental health support [12].

Cognitive behavioural therapy (CBT) has been shown to be efficacious in the treatment of depressive disorders [13, 14] and anxiety disorders [15, 16], and can be regarded as first-line treatment in children and adolescents [17]. With regard to symptoms of depression and anxiety in chronic somatic conditions, CBT has also been found to reduce symptoms of depressive disorders in adults with chronic somatic conditions [18–20], while the evidence on the effectiveness of CBT in AYA with somatic-mental health comorbidities is limited. Moreover, the access to treatments is limited. In a German sample, less than 30% of AYA with relevant mental health disturbances used mental health care offers (consulted a psychologist, psychiatrist, or psychotherapist) in the past 12 months [21]. Especially amongst AYA with chronic somatic conditions, the high prevalence rates of mental health problems combined with the very low treatment utilization rate show that methods to identify and disseminate empirically validated treatments of these disorders in health care are necessary [22, 23].

Internet- and mobile-based cognitive behavioural therapy (iCBT) might be a promising approach to overcome this mental health care gap and allow for a timely treatment of comorbid mental burden. Advantages of Internet- and mobile-based interventions include temporal and local flexibility, widespread accessibility, presumed cost-effectiveness, and low-threshold access to address psychological aspects of chronic conditions [24, 25]. iCBT, designed as self-help interventions with no or only very limited therapeutic guidance, can improve depressive symptoms and symptoms of various anxiety disorders in adults [26–29]. Several recent systematic reviews and meta-analyses indicate that iCBT is particularly efficacious when provided as therapeutically guided iCBT [30, 31]. As such, Internet- and mobile-based, therapeutically guided CBT can be as efficacious as face-to-face CBT for the treatment of mental disorders [32]. Thereby, iCBT might not only be efficacious but also safe and cost-effective. A recent meta-analysis of individual participant data showed that guided iCBT for adults with depression is associated with a mean reduced risk for symptom deterioration compared to other control conditions [33]. The results of a systematic review on cost-effectiveness indicate that guided Internet- and mobile-based interventions for the treatment of depression symptoms have the potential to be cost-effective [24]. This has also been shown for anxiety symptoms [34]. Also in this complex subpopulation of patients with somatic conditions, a systematic review reported that computerized CBT could also improve symptoms of anxiety and depression [35]. Another meta-analysis reported small to large effect sizes of iCBT on depression (*g* = −.20), anxiety symptoms (*g* = −.21), and physical health symptoms (*g* = − 1.14) within adults with somatic conditions [36]. Internet- and mobile-based interventions can also be used for the (co-)treatment of chronic somatic conditions, e.g. to increase disease-specific self-efficacy in patients with diabetes (*d* = .23) or improve pain-related disability in patients with chronic pain [37, 38].

When it comes to iCBT for AYA, the evidence is far less comprehensive. Still, current evidence suggests that iCBT can be efficacious in the treatment of anxiety and depression in AYA, again probably with higher effect sizes for guided iCBT compared to completely unguided self-help iCBT [31, 39]. However, whether this general conclusion holds true for the subpopulation of AYA with chronic somatic conditions is largely unknown; there are only a few small efficacy trials with some methodological flaws (e.g. high risk of bias due to inadequate blinding, lack of published protocols, incomplete outcome data) [40]. Thus, the effectiveness and cost-effectiveness of embedding iCBT for depression and anxiety in routine collaborative paediatric somatic care still need to be established.

## Methods/design

### Objectives

This trial aims to evaluate the effectiveness and cost-effectiveness of youthCOACH_CD_, a guided iCBT for AYA with type 1 diabetes, cystic fibrosis, or juvenile idiopathic arthritis.

The primary objective is:
To evaluate the short-term effectiveness of iCBT in improving depression and anxiety symptoms, assessed using the Patient Health Questionnaire Anxiety and Depression Scale (PHQ-ADS), at 12 weeks post-randomization (t2) compared to enhanced treatment as usual (TAU+).

Secondary objectives of the study are:
2)To evaluate the middle (t3; 6 months post-randomization) and long-term (t4; 12 months post-randomization) effectiveness of iCBT in improving depression and anxiety symptoms compared to TAU+.3)To evaluate the short (t2), middle (t3), and long-term (t4) effectiveness of iCBT compared to TAU+ in improving (a) health-related quality of life, (b) coping strategies, (c) self-efficacy, (d) stress-related growth, (e) social support, (f) behavioural activation, (g) adjustment and trauma-focused symptoms, and (h) automatic thoughts and also to evaluate the (i) working alliance and (j) intervention satisfaction in the intervention group.4)To examine the cost-effectiveness of iCBT compared to TAU+ over a period of 12 months.5)To evaluate the safety of iCBT by examining potential adverse events compared to TAU+.6)To explore potential moderators and mediators of intervention effects.

### Study design

This is a two-armed, multicentre parallel randomized controlled trial (RCT) comparing iCBT to TAU+. The intervention group receives iCBT in addition to treatment as usual (TAU). Assessments will take place starting with mental health screening in paediatric units followed by five assessment points over one year: baseline (t0), 6 weeks (t1), 3 months (t2), 6 months (t3), and 12 months (t4) post-randomization. The flow chart of the study design is shown in Fig. 1.

**Fig. 1 Fig1:**
[figure not shown]
Flow chart of inclusion and study procedure (youthCOACH_CD_ = Internet- and mobile-based cognitive behavioural therapy)

This clinical trial has been approved by the Ethics Committee of Ulm University (number 292/18) and will be conducted and reported in accordance with Consolidated Standards of Reporting Trials (CONSORT) statements for RCTs [41, 42] as well as the guidelines for executing and reporting Internet intervention research [43]. This trial will be monitored by an independent Data and Safety Monitoring Board (DSMB; CK, LK, [name]) and has been carefully checked for data protection compliance. This study protocol is in accordance with the Standard Protocol Items: Recommendations for Interventional Trials (SPIRIT) guideline [44]. The SPIRIT checklist is provided as Additional file 1.

### Participants and procedure

#### Inclusion and exclusion criteria

AYA between 12 and 21 years of age with type 1 diabetes, cystic fibrosis, or juvenile idiopathic arthritis and elevated anxiety and/or depression symptoms (Generalized Anxiety Disorder Screener, GAD-7 [45] and/or PHQ-9 [46] score ≥ 7) with Internet access and a basic knowledge of the German language are eligible for inclusion. AYA with increased risk of suicidality at screening (PHQ-9 Item 9 > 1) will be excluded for ethical and safety reasons and will receive adequate care within the ongoing clinical routine. Prior to participation, consent to study participation must be given by the AYA or, for adolescents under the age of 16, by a person with custody. As this is a pragmatic RCT, there are no further exclusion criteria.

#### Recruitment

Recruitment start is scheduled for October 2019. The iCBT with its associated independence of space and time enables a recruitment strategy throughout Germany. Anxiety and depression will be screened as part of the clinical routine in hospitals, clinics, medical practices, and medical centres across Germany where AYA with type 1 diabetes, cystic fibrosis, or juvenile idiopathic arthritis receive medical treatment. These clinical institutions are all organized within three well-established German patient registries, the National Paediatric Rheumatologic Database (NPRD) [47], the National Diabetes Registry (DPV) [48], and the Cystic Fibrosis (CF) Registry [49]. The screening data will be gathered in clinical centres and administered within these patient registries. AYA receive feedback on their mental well-being by their health care provider in charge. If AYA show anxiety and/or depression symptoms (GAD-7 [45] and/or PHQ-9 [46] score ≥ 7) without elevated suicidality (PHQ-9 Item 9 ≤ 1), the respective patient is informed by the treating physician at the clinical centre and invited to participate in the study in addition to receiving standard care/TAU. The informed consent will be obtained at the clinic by the attending physician, and all further recruitment activities will be conducted by researchers at Ulm University. For each randomized AYA the respective clinical unit receives €230 as financial compensation for its recruitment effort. Additional study information is provided on https://coach.klips-ulm.de.

#### Randomization

The participants are randomized by the program Sealed Envelope (www.sealedenvelope.com) in an allocation ratio of 1:1 using block randomization. The block size is 6, 8, 10 participants per block and stratified according to the three chronic somatic conditions. Stratification is performed due to the strongly varying prevalence of chronic somatic conditions. Only RR, who is not involved otherwise in the trial process, will conduct the randomization process. AG, FL (study administration), and MM (statistical evaluation) are blinded and do not receive any information about the group allocation of study participants. The blinded members of the study team do not have access to documents showing group membership of participants.

### Study interventions

#### Intervention condition

The intervention group receives the iCBT plus treatment as usual (TAU) and is compared to a control group, which receives TAU+. youthCOACH_CD_, developed by the Department of Clinical Psychology and Psychotherapy (FL, AG, MD, HB) consists of an introductory session with information about the online-based intervention and seven modules of approximately 50 to 70 min processing time each. Modules can be repeated as often as desired. The modules cover the topics motivation and resources, behavioural activation, understanding and coping with anxiety and depression, emotion regulation, communication, and social support as well as relapse prevention. The intervention is presented via information texts, videos, audio recordings, photos, metaphors, and therapeutic homework. The content of the intervention is based on CBT principles for depression and anxiety, including elements of psychoeducation, individual resources of the AYA, active coping (problem solving), restructuring of stressful disease-related thoughts, communication training, relaxation, and behaviour activation to model adaptive coping strategies.

The content of the intervention (see Table 1) is developed for AYA and related to typical challenges and tasks of a life with a chronic somatic condition. The intervention is explained and presented in a youth-friendly manner. To improve patient adherence, interactive elements (e.g. conditional contents, certificates) are implemented, and reminders of the weekly intervention lessons as well as homework assignments are forwarded via a mobile app. The theoretical skills learned in youthCOACH_CD_ can be tested in practice and transferred into everyday life through homework (e.g. diaries), also via a mobile app. At the beginning of the intervention, participants are informed to receive daily reinforcing prompts via a mobile app during the intervention period. The reminders are sent automatically after each module has been completed and coordinated with intervention content to transfer the learned skills into everyday life of the participants. The mobile-based reminders aim to increase motivation of participants, remind participants to complete homework assignments, and repeat intervention content. The software solutions for the iCBT intervention and the mobile app are both provided by Minddistrict (www.minddistrict.com). Access to the iCBT intervention and the app is granted through an individual username-password combination and will be available on a 24/7 basis.

**Table 1 Tab1:** Intervention content, based on cognitive behavioural therapy (CBT)

	Content	
Introduction: Welcome!	Dealing with online training Schedule, structure, and content of online training Introduction of the e-Coach	
1. Get to know your strengths!	Creating goals Becoming aware of strengths and abilities Use of own traits Techniques to build robust self-esteem Dealing with challenges/learning problem-solving skills	Mood diary
2. Become active!	Psychoeducational information on the relationship between mood and behaviour Exploring activities that give pleasure Daily structuring to reduce stress Integration of physical activity into daily life	
3. Overcoming fears	Psychoeducational information on anxiety Reduction of anxiety	
4. Learn to deal with bad moods	Psychoeducational information on depression Recognition and handling of rumination and dysfunctional thoughts Activation	
5. Recognize and understand very strong feelings!	Psychoeducational information on emotions Acceptance of emotions Dealing with very strong feelings (e.g. skills, relaxation techniques)	
6. Together we are stronger!	Social competence training Communication skills Perception of social support Increasing personal responsibility	
7. You did it!	Summary of the learned contents Coping strategies and support Information on further treatment options regarding mental health	

#### Guidance

The intervention is therapist-guided by e-Coaches, who report semi-standardized feedback after each completed module on the intervention platform to the participant using an e-Coach manual. The e-Coach manual is standardized to guarantee protocol adherence by the e-Coaches. e-Coaches are graduates of a Master’s Degree in Psychology or Pedagogy, who are enrolled in a training program in CBT with children and adolescents, closely supervised by licensed psychotherapists. The feedback content matches the participants’ tasks and is aimed to support adherence to treatment. The feedback also includes positive reinforcement to motivate participants to continue the intervention. For further questions, participants and e-Coaches can communicate via the intervention platform. e-Coaches will also send reminders to participants who do not complete intervention modules at the scheduled time via e-mail and telephone. The weekly schedule for processing a module is set by the participants themselves at the end of the previous module. In order to promote commitment, the intervention is blocked for the participant after three reminders without the participant reacting. For participants who indicate that they wish to continue, youthCOACH_CD_ will be reactivated. Table 2 shows the intervention structure and implementation.

**Table 2 Tab2:** Intervention structure, technical implementations, and support

Intervention structure	
• Seven weekly modules (50-70 min.)	
Implemented elements	
• Guidance by trained and supervised e-Coaches (graduates of a Master’s Degree, who are enrolled in a training program in CBT with children and adolescents)	
• One feedback message per module by e-Coaches	
• Reminders by the e-Coach if the modules are not processed at a date set in advance by the participant to promote adherence	
• Deactivation and reactivation when modules are not processed and three unsuccessful reminders	
• Answers to additional questions from e-Coaches and the study team	
• Tight security procedure for suicidal clues	
• Weekly challenges/ homework	
• Diaries via a mobile app with daily reminders	
• Information given by text and videos	
• Audio guided exercises	
• Patient examples written and presented as audio recordings	
• Metaphors, quizzes and conditional content	
• Modules can be repeated as often as desired	

#### TAU+

TAU+ includes all routine care services for somatic and mental health problems. TAU+ can vary depending on the clinic, location, care options, and barriers of care as well as the specific needs of AYA. TAU is supplemented (enhanced, +) by screening for symptoms of anxiety and depression and by information letters on evidence-based mental health care options.

TAU+ is not defined a priori, but is recorded alongside the health economic evaluation and can thus be described post hoc descriptively.

### Sample size/power calculation

A clinically significant effect of at least *d* = .50 for the mean difference between the groups is assumed, which refers to the severity of the primary outcome, i.e. a PHQ-ADS sum score [50] at 12 weeks post-randomization (t2). The assumption for the clinically significant effect is based on a meta-analysis by Ebert and colleagues, who reported a moderate to high effect size of *g* = .72 (95% confidence interval [CI] .55–.90) for Internet and computer-based CBT in the reduction of depressive and anxiety symptoms in youth [39], based on trials comparing Internet- and computer-based CBT to non-active control conditions (waitlist; placebo). However, given that TAU usually results in higher effect sizes compared to waitlist control groups, we regard a lower than *g* = .72 effect size as clinically relevant. The sample size calculation was carried out by an external statistician from the Department of Psychological Research Methods at Ulm University (MM) based on a power of .90 and α < .05 (two tailed) considering the cluster structure (intra-class correlation [ICC] = .02) of the different prevalence numbers of these chronic somatic conditions, resulting in 166 participants equally randomized to both conditions (2 × *n* = 83). According to a meta-analysis, studies evaluating the efficacy and effectiveness of computer-based psychological treatments for depression with therapeutic support reported a drop-out rate of approximately 28% [51]. For this reason, the sample is increased by 28%, resulting in a total of *N* = 212 participants (2 × *n* = 106).

Various measures will be taken to minimize study drop-outs. Participants receive €10 as an expense allowance at all psychometric assessment points. After successful completion of all assessments, participants can also take part in a prize draw. Moreover, in order to avoid drop-outs in the intervention group, youthCOACH_CD_ was designed to persuade the target group of AYA using e.g. multimedia features such as videos and audios as well as prompts and reminders [52].

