## Discussion

The aim of this study is to examine the (cost-)effectiveness of youthCOACH_CD_, an iCBT for AYA with a chronic somatic condition and comorbid depressive and/or anxiety symptoms.

The innovative aspects of the study are the following: (1) youthCOACH_CD_ is implemented directly into routine medical care. As such, the present study will provide important insights for health care policy on how to integrate iCBT into our health care systems. (2) Studies show that AYA between the ages of 12 and 25 spend an average of 22 h a week online with an increasing tendency to communicate, play, or entertain. Four out of five of 12- to 17-year-olds (80.6%) have used the Internet daily in the last 12 months [98]. Only 4.6% of adolescents at this age do not make use of the Internet. The fact that AYA grow up as digital natives could make online use of an intervention well accepted.

Continuing with advantages, the methodical strengths of the study are as follows: (3) The area-wide recruitment via the German patient registers enables a representative sample and facilitates generalization. (4) With a target sample of 212 adolescents, the study will be high-powered (1 – β = .90). (5) In addition to self-report questionnaires, the study also includes caregiver self-reports on their perception of participants’ conditions. This provides further insights into the effectiveness of iCBT. (6) Not only the effectiveness of youthCOACH_CD_, but also undesirable potential adverse events will be investigated in detail in this study. (7) As one of as yet only a few clinical trials on psychological interventions for AYA with chronic somatic conditions and symptoms of depression and anxiety, the present RCT also comprises cost-effectiveness analyses. (8) Finally, in addition to the psychological parameters, medical data are collected, which are linked to each other and thus allow deeper insights into comorbidity.

The study has several possible obstacles and limitations. First, adolescents aged 12 to 16 years need the informed consent of the custodial persons to participate in the study. This legal constraint might lead to a left-skewed age distribution of the study participants. By adjusting the covariate baseline to age, sex, and chronic somatic disease, this possible limitation is taken into account in the statistical analysis.

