Second, intervention and study adherence might be limited in AYA, as has been reported before [99]. Therefore, a drop-out rate of 28% was established. As a counterstrategy we developed our intervention based on persuasive design aspects and provide it therapeutically guided—measures that are associated with improved intervention adherence [51, 100]. Additionally, participants receive a monetary compensation for their study efforts, which will likely increase study adherence.

Third, participant inclusion is based on depression/anxiety symptoms and not on mental disorder status. The reason for this is that the assessments are based on participants’ self-report, which is complemented by caregiver reports. Therefore, participants, caregivers, and physicians of the recruitment supporting clinics are informed that youthCOACH_CD_ is designed as a (guided) self-help intervention that does not replace on-site mental health care according to existing guidelines in case of manifest mental disorders.

Fourth, given the nature of the present trial, participants need to go through several self-report assessments. This might bias effectiveness results in two ways. On the one hand, the assessments might lead to a self-selection of participants with only those being randomized who are determined enough to finalize a comprehensive baseline assessment. At the same time, reminders on the follow-up assessments might have an intervention adherence facilitating effect, reminding participants not only to conduct the assessments but to continue the intervention or reminding them e.g. of learned intervention aspects. On the other hand, the comprehensive assessment with several self-report questionnaires might have a negative effect on trial adherence, increasing attrition rates. These not yet well examined and understood research biases on intervention effects inherent to RCTs need to be taken into account when interpreting the coming effectiveness findings.

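### The 28% drop-out allowance is multiplied on instead of divided out, so the printed calculation supports about 87% power for 212 participants, not 90%

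*Protocol article*

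**What the plan says.** In the Protocol article, the section Sample size/power calculation sets the target effect: "A clinically significant effect of at least *d* = .50 for the mean difference between the groups is assumed". This refers to the PHQ-ADS sum score at 12 weeks (t2). The calculation is "based on a power of .90 and α < .05 (two tailed"), "considering the cluster structure (intra-class correlation [ICC] = .02"]), and its outcome is given as "resulting in 166 participants equally randomized to both conditions (2 × *n* = 83"). Randomization confirms equal arms: "in an allocation ratio of 1:1 using block randomization".

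The same section cites a drop-out rate of about 28% from a meta-analysis of therapist-supported computer-based treatments for depression. It continues "For this reason, the sample is increased by 28%, resulting in a total of" 212 (2 × 106). Drop-out is the only reason given for the increase.

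The Discussion adopts the rate for this trial: "Therefore, a drop-out rate of 28% was established". It also lists the power among the trial's methodological strengths, with 1 − β = .90 attached: "With a target sample of 212 adolescents, the study will be high-powered".

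**The concern.** An allowance for drop-out should leave the required number once the expected loss has occurred. Adding 28% to the required number does not do this, because the 28% is then lost from the larger, randomised number. The plan needs 166 participants with the outcome, and its own loss rate leaves fewer than that out of 212.

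What is at stake is the meaning of the printed .90. If the trial finds no difference, readers will judge that result partly by the stated power, and that power belongs to more observed outcomes than the plan expects to have.

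**Working it through.** **Inputs, all from Sample size/power calculation unless noted**
- d = .50, two-sided α = .05, power .90
- ICC = .02; the article gives no cluster number, cluster size or design-effect formula
- required: 166 (83 per arm), allocated 1:1 (Randomization)
- drop-out: 28% (also Discussion)
- randomised: 212 (106 per arm)

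**Step 1. The plan's 166.** The normal approximation per arm is 2 × (1.960 + 1.282)² / 0.50² = 84.06, rounded up to 85, or 170 in total. The t-based figure is 85.03 per arm. The stated 166 is close to both. Multiplying by 1 − ICC gives 170 × 0.98 = 166.6, which may be how 166 arose; this is an assumption, because the article shows no formula. The 166 is accepted as given below.

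**Step 2. The plan's 212.** 166 × 1.28 = 212.48, and 83 × 1.28 = 106.24. These give the stated 212 and 106. Division does not: 166 / 0.72 = 230.6.

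**Step 3. What 212 leaves.**
- 212 × (1 − 0.28) = 152.6 with an observed t2 score, about 76 per arm
- shortfall: 166 − 152.6 = 13.4, about 13 to 14 participants
- loss that 212 can absorb: 1 − 166/212 = 21.7%
- number that retains 83 per arm: 83 / 0.72 = 115.3, so 116 per arm and 232 in total

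**Step 4. Power at d = .50, two-sided .05.** The normal approximation is Φ(d × √(n/2) − 1.96), with n per arm. For 76 per arm: 0.5 × √38 = 3.082, and Φ(3.082 − 1.960) = .869. The t version uses the noncentral t distribution. The last two rows multiply the variance by 0.98, the assumed ICC handling from Step 1.

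| Method | 83 per arm | 76 per arm | Difference |
|---|---|---|---|
| t-test | .893 | .865 | .028 |
| Normal | .896 | .869 | .027 |
| t-test, variance × 0.98 | .899 | .872 | .027 |
| Normal, variance × 0.98 | .902 | .876 | .026 |

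The loss due to the drop-out step is therefore about 2.7 points on every scale. On the plain t-test the rest of the gap to .90 is already there at 83 per arm (.893). The effect detectable with 90% power (t-test) moves from .506 at 83 per arm to .529 at 76 per arm.

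**Step 5. What baseline adjustment could add.** The primary model (Effectiveness analysis) has baseline PHQ-ADS as a covariate. With a baseline–t2 correlation r, the residual variance is multiplied by 1 − r². The article gives no r, so a range is shown for 76 per arm (t-test scale):

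| Assumed r | Power |
|---|---|
| 0 | .865 |
| .30 | .894 |
| .33 | .900 |
| .40 | .916 |
| .50 | .943 |

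**The case against.** **All 212 will be analysed.** A reader might infer that the trial will analyse only about 152 people. The documents do not support that: Effectiveness analysis specifies intention-to-treat and Statistical analyses specifies multiple imputation, so all 212 enter the model. About 152 is the expected number with an observed t2 score. This corrects the description without removing the problem. Imputation from earlier scores does not in general restore the information in the missing outcomes, and the plan inflated the sample because it expects that loss.

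**The planned analysis may reach 90% anyway.** A reader might infer that the trial will in fact fall short of its stated power. That is too categorical. As Step 5 shows, a baseline–t2 correlation of about .33 is enough with 76 per arm, and the planned model could collect that gain. However, the sample-size section names no correlation and takes no credit for one. The .90 is not supported by the calculation as printed; whether the planned analysis reaches it cannot be known from the document.

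**The 28% may not be loss of the t2 outcome.** The article does not say whether the cited rate means leaving treatment or missing assessments, or at what time. Someone who stops the modules can still complete the t2 questionnaire, and the plan lists payments and a prize draw to retain participants. If t2 loss is at most 21.7%, 166 outcomes remain. This is a fair caution about what will happen. It does not rescue the calculation, which itself treats the 28% as loss from the required sample.

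**The effect is small.** This stands. Power near 87% is still reasonable, the target effect is stated as a minimum, and type I error, bias and the analysis itself are untouched. The planned 95% confidence intervals will show the precision actually achieved. The point is therefore not a serious defect of the trial.

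**Conclusion.** The slip is confirmed: 212 arises only as 166 × 1.28, and a 28% loss would need 230.6, or 232 with equal arms. With 212 randomised and 28% drop-out, about 152 participants have an observed t2 score, 13 to 14 fewer than required. The stated calculation then supports about 86.5% to 87.6% power at d = .50 instead of .90, and about 2.7 points of power are due to this step.

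This rests on three assumptions: the 28% applies to the t2 outcome, as the plan's own use of it implies; imputation adds no material information; and no credit is taken for baseline adjustment, as in the printed calculation. The upper end of the range also assumes that the ICC entered as a variance factor of 0.98. The correction should be made, but it is modest and does not put the trial's validity in question.

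**What to change.** Keep 212 and correct the derivation in Sample size/power calculation to N / (1 − drop-out rate). Then state one of the following:

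1. with 212 randomised and 28% drop-out, about 152 observed t2 scores are expected, giving roughly 87% power at d = .50; or
2. 212 gives 90% power only if drop-out is at most about 22%; or
3. 90% power is claimed for the baseline-adjusted model, with the assumed baseline–t2 correlation stated and justified (about .33 or more with 76 per arm).

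Change the .90 attached to 212 in the Discussion to match. Under option 1 or 2 the cost is a slightly less favourable or a conditional power statement; under option 3 it is the need to justify the correlation. No extra patients and no change to the analysis are needed. Randomising 232 would also resolve the point, at the price of 20 more participants, but the size of the shortfall does not require it.
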